# **Synopsis**

| Title of Study | Efficacy Study of L-arginine in Patients with HTLV-1 Associated Myelopathy |
| --- | --- |
| Primary Objective | Change in 10-meter walking time from Day 0 to Day 7 |
| Secondary Objective | - Change in 10-meter walking time from Day 0 to Days 3 and 14 - Change in measurements obtained with the Timed Up and Go Test from Day 0 to Day 3, 7, and 14 - Degree of improvement in CSF cell count, protein, and neopterin concentration - Safety; Adverse events (nature and severity of adverse events, frequency of discontinuations and dropouts) |
| Study Drug | Argi U® Combination Granules |
| Active Ingredient | L-Arginine hydrochloride and L-Arginine |
| Number of Patients | 20 patients will be recruited |
| Study Entry Criteria | HTLV-1 associated myelopathy/Tropical spastic paraparesis (HAM/TSP)  Inclusion Criteria:   1. Patient with HAM/TSP 2. Age ≥ 20 years at the time of consent 3. Ongoing medication for HAM/TSP, with no changes in 12 weeks before enrollment. Subjects on maintenance therapy with steroids must have been receiving ≤ 10 mg/day prednisolone equivalent continuously for at least 12 weeks before enrollment. 4. Subjects are able to walk ≥ 10 meters at screening (use of a single cane, double canes or any walking aid is allowed) 5. Voluntary written informed consent to participate in the study 6. Subjects are able to see the Kagoshima University Hospital on the schedule days   Exclusion Criteria:   1. Participation in a clinical trial within 16 weeks before informed consent 2. 10-meter walking time at screening has changed more than 30% compared with 10-meter walking time within 8 weeks before consent (data of all the days when visiting multiple days) 3. Any of the following significant concomitant diseases; Poorly controlled diabetes mellitus, Heart failure, Severe chronic lung disease requiring oxygen therapy, Renal failure, Liver dysfunction 4. Active malignancy or past history of malignancy (with the exception of resected or surgically cured solid cancer, with no recurrence of the cancer more than 3 years before informed consent, and resected intra-epithelium carcinoma of cervix cancer, uterine body or digestive ducts) 5. Adult T cell leukemia/lymphoma 6. Pregnant, breastfeeding or possible pregnant. Subjects without agree to contraception during the study period. 7. Concurrent spinal cord compression lesion (e.g., cervical spine disease and ossification of the yellow ligament) with the exception of conditions that would not affect evaluating 10-meter walking test in the study, as judged by the investigator 8. Concurrent diseases that markedly impair brain function such as psychiatric disorder, epilepsy, dementia, Parkinson’s disease, cerebrovascular disease 9. Bone fracture within 24 weeks before informed consent 10. Any other condition unsuitable for participation in the study in the opinion |

# **Background**

Since the retrovirus HTLV-1 cannot be eliminated from HTLV-1 carrier patients, HAM/TSP is thought to be a lifelong inflammatory condition once it develops. Therefore, therapeutic agents for HAM/TSP are required to continuously control the inflammation caused by the virus. In this respect, long-term administration of corticosteroids is reasonable, as the drug is used in some other chronic autoimmune diseases. However, the steroids show small therapeutic benefit, and continuing the treatment is difficult to tolerate due to various side effects including diabetes and osteoporosis. Since HAM/TSP requires lifelong treatment, there is a need for treatment with inexpensive and safe drugs. In this context, we have experienced cases of improvement in gait disturbance in several HAM/TSP patients treated with L-arginine. In addition, CSF neopterin level also improved in the patients. Treatment with amino acids may be an inexpensive and safe way to treat the patients with HAM/TSP. However, there is no evidence that L-arginine is effective in treating the patients, and clinical studies are needed to confirm its efficacy.

# **Trial Objectives**

There are only a few effective treatments for HAM/TSP, and we will search for a safe, inexpensive, and long-term oral treatment. We will conduct an open study in a small number of patients to confirm the efficacy and safety of Argi U® (L-arginine), which is already approved for the treatment of amino acid metabolism disorders, for patients with HAM/TSP.

## **Primary Objective**

Change in 10-meter walking time from Day 0 to Day 7.

## **Secondary Objectives**

- Efficacy
- Change in 10-meter walking time from Day 0 to Days 3 and 14.
- Change in measurements obtained with the Timed Up and Go Test from Day 0 to Day 3, 7, and 14.
- Degree of improvement in CSF cell count, protein, and neopterin concentration
- Safety
- Adverse events (nature and severity of adverse events, frequency of discontinuations and dropouts)

# **Inclusion/Exclusion Criteria**

## **Eligibility Criteria**

Target disease; HTLV-1 associated myelopathy/Tropical spastic paraparesis：HAM/TSP (Diagnostic criteria according to World Health Organization conference at Kagoshima in 1988)

## **Inclusion Criteria**

Subjects eligible for enrollment in the study must meet all of the following criteria:

1. Patient with HAM/TSP
2. Age ≥ 20 years at the time of consent
3. Ongoing medication for HAM/TSP, with no changes in 12 weeks before enrollment. Subjects on maintenance therapy with steroids must have been receiving ≤ 10 mg/day prednisolone equivalent continuously for at least 12 weeks before enrollment.
4. Subjects are able to walk ≥ 10 meters at screening (use of a single cane, double canes or any walking aid is allowed)
5. Voluntary written informed consent to participate in the study
6. Subjects are able to see the Kagoshima University Hospital on the schedule days

## **Exclusion Criteria**

1. Participation in a clinical trial within 16 weeks before informed consent
2. 10-meter walking time at screening has changed more than 30% compared with 10-meter walking time within 8 weeks before consent (data of all the days when visiting multiple days)
3. Any of the following significant concomitant diseases; Poorly controlled diabetes mellitus, Heart failure, Severe chronic lung disease requiring oxygen therapy, Renal failure, Liver dysfunction
4. Active malignancy or past history of malignancy (with the exception of resected or surgically cured solid cancer, with no recurrence of the cancer more than 3 years before informed consent, and resected intra-epithelium carcinoma of cervix cancer, uterine body or digestive ducts)
5. Adult T cell leukemia/lymphoma
6. Pregnant, breastfeeding or possible pregnant. Subjects without agree to contraception during the study period
7. Concurrent spinal cord compression lesion (e.g., cervical spine disease, ossification of the yellow ligament) with the exception of conditions that would not affect evaluating 10-meter walking test in the study, as judged by the investigator)
8. Concurrent diseases that markedly impair brain function such as psychiatric disorder, epilepsy, dementia, Parkinson’s disease, cerebrovascular disease
9. Bone fracture within 24 weeks before informed consent
10. Any other condition unsuitable for participation in the study in the opinion of the investigator

## **Subjective Discontinuation Criteria**

This clinical study will be discontinued if serious side effects beyond the expected range are observed with medication, or if it can be determined that the study drug is clearly ineffective. As this is a clinical study involving a small number of patients, data related to this study will be analyzed after discontinuation to provide basic information for clarifying the causes of adverse events.

# **Study Design and Plan**

## **Study Design**

An open interventional study of Argi U® (L-arginine) orally for 7 consecutive days to confirm safety and efficacy in a single group of HAM/TSP patients without a placebo or control group.

## **Study Schedule**

### **Screening**

The principal investigator or sub-investigator will assign a screening number (HAM-SCR01~) to each subject whose consent has been obtained, conduct a screening test to confirm eligibility, and investigate that there are no problems with inclusion in this study. The screened cases will be listed in the screening roster. The principal investigator or sub-investigator will enroll the subjects whose eligibility has been confirmed by the screening test into this study. The study phases are described below and a schedule are displayed in Table 1.

### **Treatment Phase**

- Study drug administration (Day 1)

The principal investigator or sub-investigator will confirm that there are no problems with the administration of the study drug based on the test results at the time of admission. Confirm that the disbursed drugs are taken appropriately.

- Discharge from the hospital (Day 14)

The investigator or sub-investigator will continue to evaluate the efficacy and safety of the drug after the end of the administration period.

- Termination and discontinuation (Day 28)

The principal investigator or sub-investigator will conduct an exit examination on Day 28. If events requiring follow-up or adverse events persist during the exit examination, they shall be followed until safety is confirmed.

## **Unexpected Exacerbation**

In the event of an unexpected exacerbation during this clinical study, the following treatments will be provided in consultation with the patient

- Oral or intravenous corticosteroid therapy

Adverse events: Diabetes, osteoporosis, immunosuppression, gastric and duodenal ulcer, etc.

- Interferon alpha injection therapy

Adverse events: Fever, chills, malaise, bone marrow suppression, anemia, dizziness, anorexia, hypoglycemia, interstitial pneumonia, liver dysfunction, rheumatoid arthritis, etc.

# **Treatment of Subjects**

## **Description of Study Drug**

Trade name: Argi U® Combination Granules

Composition: The drug contains the following ingredients in 1.3g

L-Arginine hydrochloride 605mg

L-Arginine 500mg

(Total 1000mg as L-Arginine)

This product is a white granule with no odor and a slightly peculiar taste.

## **Concomitant Medications**

Treatment during the clinical study will continue as before hospitalization, including rehabilitation. If symptoms worsen significantly during the clinical study, the study will be stopped immediately and treatment will be given according to the possible condition and cause. Changes in the dosage and administration of the following medications and treatments will not be permitted during study participation. Rehabilitation and massage should not be changed in frequency or duration.

- Other immunosuppressive drugs and steroids (except topical drugs)
- All drugs prescribed to improve its symptoms
- Rehabilitation and massage
- Health foods (supplements)

## **Prohibited Medications**

The following drugs are prohibited from the time of screening until the end of the study period.

- Injectable steroids (may be used at the discretion of the physician)
- Interferon
- Other study drugs

## **Informed Consent**

The principal investigator or sub-investigator will select candidate patients for this study, provide them with sufficient explanations using the explanation document and consent form approved by the Kagoshima University Clinical Research Review Committee, and obtain free and voluntary consent in writing from the patients themselves.

# **Study Drug Materials**

## **Study Drug**

　Trade name: Argi U® Combination Granules

　Composition: The drug contains the following ingredients in 1.3g

　L-Arginine hydrochloride 605mg

　L-Arginine 500mg

　(Total 1000mg as L-Arginine)

　This product is a white granule with no odor and a slightly peculiar taste.

　Packaging: 500g

## **Drug Administration**

The usual daily dosage is 0.15 to 0.50 g (0.12 to 0.38 g as L-arginine) per kilogram of body weight in 3 to 6 divided doses. The dosage may be adjusted according to the patient's age and symptoms. In general, start with a small dose and titrate upward until a satisfactory effect is obtained, referring to blood ammonia levels, subjective symptoms, etc.

# **Assessment of Activity**

Table 1: Schedule of Assessments

## **Primary and Secondary Endpoints**

The primary endpoint:

- Change in 10-meter walking time from Day0 to Day7

The secondary endpoints:

- Efficacy
- Change in 10m walking time between Day 0 and Days 3 and 14
- Change in measurements obtained with the Timed Up and Go from Day 0 to Day 3, 7, and 14
- Degree of improvement in CSF cell count, protein, and neopterin concentration

## **Evaluation points**

Evaluation points are described below and the schedule are displayed in Table 1.

1. Subject’s Background (Day -28)

Initials, sex, date of birth, date of initial diagnosis, date of confirmed diagnosis of HAM/TSP (year, month or year only is acceptable), medical history, treatment history, pre-existing conditions, complications, concomitant medications

1. Vital signs (Day -28, 0, 1, 3, 7, 14, 28)

Body temperature, blood pressure, pulse, height (measured only on Day-28), weight (not measured on Day 1 and 3)

1. Blood Test (Day -28, 0, 7, 14, 28)

The following items shall be measured in the hospital, and the method of measurement shall be standardized during the study period. Hematological examination (collection volume: 4ml); WBC, RBC, Hb, PLT. Blood biochemical examination (collection volume: 8ml); TP, AST, ALT, BUN, Cr, Na, K, FBS, CRP. However, anti-HTLV-1 antibody titer (CLIA method) will be measured only for Day-28 (screening), and HbA1c will be measured only for Day0 (admission). On Day0 and Day7, Day14, and Day28, HTLV-1 proviral load in PBMC (blood collection volume: 20 ml) will be measured.

The following items shall be measured in the PASOLAB, and the measurement methods shall be standardized during the research period.

Serum sIL-2R, Serum anti-HTLV-1Ab titer (CLIA) (collection volume: 10ml)

1. Blood gas analysis (conducted as necessary on Day 3) (Blood collection volume: 2 ml)

Measurement shall be performed in the hospital, and the measurement method shall be standardized during the study period.

1. Blood concentration (Day 0, 7, 14, 28)

Blood Arginine and amino acids concentration shall be measured by external testing system (BML).

1. Urinalysis (Day- 28, 0, 7, 14, 28)

Measurements shall be taken in the hospital, and the measurement method shall be standardized during the study period.

1. CSF examination (Day 0, 7) (collection volume: 5ml)

The following items shall be measured in the hospital, and the method of measurement shall be standardized during the study period.

Cell count, protein

The following items will be measured in the PASOLAB, and the measurement methods will be standardized during the study period.

CSF Anti-HTLV-1 antibody titer (CLIA method), CSF neopterin concentration, CSF CXCL10

1. 10-meter walk test (Day -28, 0, 3, 7, 14, 28)

＜Implementation Method＞

Mark the beginning and end of a 10 m straight line on the floor with tape, etc., and measure the time required for walking with a stopwatch.

If a walking aid (one-handed cane, two-handed cane, etc.) is used for walking, it will be measured without changing the aid during the study period.

The test will be conducted after a short stretching session before the walking test. (The content of stretching will be decided for each patient.)

Start walking 2 m before the starting point, and measure the time taken from the time when the patient passes the starting point to the time when the patient passes the ending point.

1. Time Up and Go Test (Day -28, 0, 3, 7, 14, 28)

＜Implementation Method＞

The starting position is leaning back lightly, with hands on thighs.

The starting posture is to lean back lightly on the backrest and place the hands on the thighs. In this case, both feet should be on the floor.

The time taken to stand up from the armchair, walk around the marker 3m away, and sit down on the chair again shall be measured. 0m point shall be the front leg of the chair, and 3m point shall be the center of the cone.

The subject is asked to perform a series of movements at "normal walking speed" and "maximum walking speed" (two times in total) following the call of the measurer.

The measurer measures the time from the time when a part of the subject's body starts to move to the time when the buttocks touch the ground. (This is not a strict rule; it should be from standing to sitting.)

After two measurements, the smaller value (faster time) shall be adopted, and the number of seconds to one decimal place shall be recorded. (The second digit shall be rounded off.)

[Precautions for measurement]

If a walking aid is used in daily life, it should be used as it is. If you use a walking aid in your daily life, use it as it is.

The way the subject turns the cone is up to the subject.

When the subject goes around the cone, there is a high risk of falling, and when the subject sits down, there is a risk of falling due to excessive momentum, so the measurer should be careful. (Be especially careful on tatami mats, as they are slippery.)

1. OMDS (Day -28, 0, 3, 7, 14, 28)

<Implementation methods>

The patient’s condition will be determined according to the table below and scored.

| Grade | Motor Disability Grade |
| --- | --- |
| 0 | Normal gait and running |
| 1 | Normal gait but runs slowly |
| 2 | Abnormal gait (staggering or spastic) |
| 3 | Unable to run |
| 4 | Need handrail to climb stairs |
| 5 | Needs a cane (unilateral support) to walk |
| 6 | Needs bilateral support to walk |
| 7 | Can walk 5-10m with bilateral support |
| 8 | Can walk 1-5m with bilateral support |
| 9 | Cannot walk, but able to crawl |
| 10 | Cannot crawl, but able to move using arms |
| 11 | Cannot move around, but able to turn over in bed |
| 12 | Cannot turn over in bed |
| 13 | Cannot even move toes |

1. Modified Ashworth Scale (Day -28, 0, 3, 7, 14, 28)

The patient’s condition will be determined according to the table below and scored.

| Grade | Description |
| --- | --- |
| 0 | No increase muscle tone |
| 1 | Slight increase in muscle tone, manifested by a catch and release or by minimal resistance at the end of motion when the affected part(s) in moved in flexion or extension |
| 1+ | Slight increase in muscle tone, manifested by a catch, followed by minimal resistance throughout the remainder (less than half) of the ROM |
| 2 | More marked increase in muscle tone through most of the ROM, but affected part(s) easily moved |
| 3 | Considerable increase in muscle tone, passive movement difficult |
| 4 | Affected part(s) rigid in flexion or extension |

1. OABSS (Day -28, 0, 3, 7, 14, 28)

The following questionnaire will be used to survey the period from the date of the last response to today.

| Question | Frequency | Score |
| --- | --- | --- |
| Q1. How many times do you typically urinate from walking in the morning to going to sleep at night? | 7 or less | 0 |
|  | 8-14 | 1 |
|  | 15 or more | 2 |
| Q2. How many times do you typically wake up to urinate at night? | None | 0 |
|  | 1 | 1 |
|  | 2 | 2 |
|  | 3 or more | 3 |
| Q3. How often do you have a sudden desire to urinate that is difficult to defer? | None | 0 |
|  | Less than once a week | 1 |
|  | Once a week or more | 2 |
|  | About once a day | 3 |
|  | 2-4 times a day | 4 |
|  | 5 times a day or more | 5 |
| Q4. How often do you leak urine because you cannot defer the sudden desire to urinate? | None | 0 |
|  | Less than once a week | 1 |
|  | Once a week or more | 2 |
|  | About once a day | 3 |
|  | 2-4 times a day | 4 |
|  | 5 times a day or more | 5 |

1. Assessment of pain and numbness using VAS (Day -28, 0, 3, 7, 14, 28)

For the period from the time of the last evaluation to today, ask the patient to write the severity of the problem on a line 10 cm long. (0 at the left end: "No pain (numbness)", 10 at the right end: "Pain (numbness) is at its worst")

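### The Timed Up and Go clock rule is declared non-strict and the walking aid is not fixed across visits, so a secondary endpoint based on within-patient change rests on a task that is not held constant

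*Protocol*

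**What the plan says.** All the measurement rules are in protocol Section 8.2 (Evaluation points).

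- **Task.** The TUG begins seated, with both feet on the floor, the back against the backrest and hands on thighs. "The time taken to stand up from the armchair, walk around the marker 3m away, and sit down on the chair again shall be measured".
- **Clock rule.** The measurer times "from the time when a part of the subject's body starts to move to the time when the buttocks touch the ground".
- **Qualification.** The parenthesis that follows reads "This is not a strict rule; it should be from standing to sitting".
- **Recording.** Times are kept to one decimal place of a second.
- **TUG aid.** "If a walking aid is used in daily life, it should be used as it is". No sentence holds the aid constant across visits.
- **10-meter walk aid.** For a patient who walks with an aid, "it will be measured without changing the aid during the study period".

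Section 8.1 makes TUG change from Day 0 to Days 3, 7 and 14 a secondary efficacy endpoint. Section 5.1 describes an open study in one group with no placebo or control.

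**The concern.** The endpoint is a difference between two stopwatch readings on the same patient. It measures change in the patient only if both readings cover the same interval of the same task. Here the only operational definition of the interval is followed at once by a statement that it need not be applied strictly, with a differently worded interval offered beside it. The aid, which can itself alter the time, is fixed for one timed gait test and not for the other.

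The design makes this more than a matter of style. With no concurrent control, a drift in timing between Day 0 and the on-drug visits has nothing to cancel against. The study is open and the protocol provides no measurer who is unaware of the visit, so discretion over the clock start is exercised by someone who may know whether the reading is the baseline or a follow-up.

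**Working it through.** The protocol states no figure that depends on this point. The 20 patients in Section 10.1 are justified only as a pilot size, with no effect size, standard deviation or power. The check is therefore a comparison of the texts, plus one line of algebra to show what an inconsistent clock start does.

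**1. Clock start.** Three sentences bear on it.
- The task sentence counts standing up in the measured time.
- The clock sentence starts at first movement. From the prescribed seated posture, that also includes standing up.
- The parenthesis makes the clock sentence non-strict and speaks of standing to sitting. Read literally, it leaves out the rise. Read as standing up to sitting down, it includes the rise but may start slightly later than the first movement of any body part.

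The first two agree. The third loosens them, and nothing elsewhere in the protocol restores a fixed start.

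**2. Clock stop.** The clock sentence ends when "the ground" is touched, in the protocol's wording ("starts to move to the time when the buttocks touch the ground"). The task sentence has the patient sit down on the chair, so the intended stop is clear.

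**3. Aid.** The 10-meter walk has an explicit no-change rule. The TUG has only the daily-life rule, stated twice in near-identical words. A patient whose daily aid changed could be tested with different aids at two visits without breaching the TUG text.

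**4. Effect on the change score.** Let *g* be the stretch of time between the earlier and the later permitted start, and Δ the true change in the full task from Day 0 to a later visit.
- Same start at both visits: no artificial shift from switching starts.
- Earlier start at Day 0, later start at follow-up: recorded change = Δ − *g* (*g* taken at follow-up), a spurious improvement.
- Later start at Day 0, earlier start at follow-up: recorded change = Δ + *g* (*g* taken at Day 0), a spurious worsening.

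If a share *p* of patients falls in the second case and a share *q* in the third, with *g* treated as constant, then:
- mean error = (*q* − *p*)*g*
- added variance = [(*p* + *q*) − (*q* − *p*)²]*g*², if the switching is unrelated to Δ

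With *p* = *q* there is no bias, only noise of variance (*p* + *q*)*g*². With *p* > *q* the bias favors the drug.

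**5. Inputs available.** The documents give no value for *g*, *p* or *q*, no TUG times and no standard deviation of TUG change. The sign and size of the error cannot be obtained from them.

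**The case against.** The strongest reply is that the text, read as a whole, already points to one interval. The start posture is seated and the time to stand up is to be measured, so starting the clock on an upright patient would contradict the section. The English reads like a translation, and standing to sitting most naturally means standing up to sitting down. This largely stands. A reader might infer that the protocol prescribes two different tasks, one with the rise and one without, and that both are equally permitted. The section as a whole does not support that. What survives is narrower: even on the benign reading, the only operational rule is expressly made optional.

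On the aid, the Day 0, 3, 7 and 14 tests fall between admission and discharge (Sections 8.2 and 5.2.2). Section 6.2 forbids changes in rehabilitation frequency or duration, and the 10-meter walk on the same days already fixes its aid. A change of TUG aid in that period is therefore only a possibility. The mention of the ground is a harmless slip.

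A reader might also be tempted to put a false-positive rate on the defect. With 20 patients, a one-sided 10% level and an assumed paired t-test, a spurious shift of 0.2 or 0.3 standard deviations under an inert drug gives a positive result in 34% or 51% of trials. The arithmetic is right, but the shift, its direction and the test are all assumed. Other equally arbitrary inputs (0.5 to 2 s shorter on drug, standard deviation of change 2 to 5 s, a quarter or all of the patients shifted) give anything from 12% to over 99%. That range reflects the assumptions and does not measure this protocol's error. Nor do the documents say how much of a TUG time the rise takes in these patients.

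Finally, only a secondary endpoint of a small pilot is touched. That is true, and it limits the weight of the point. It does not remove the point, because stopwatch rules belong in the protocol and a statistical analysis plan would not normally supply them.

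**Conclusion.** The point holds in a limited form. Section 8.2 states a clock rule and then withdraws its force, and it omits for the TUG the aid rule that it states for the 10-meter walk. No other section repairs either. Because the endpoint is an uncontrolled within-patient change read by an observer who may know the visit, either gap could add noise or bias.

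The size and direction are unknown, and no error rate should be quoted as the consequence. The conclusion does not need the literal reading of the parenthesis. It rests only on the rule being called non-strict and on the aid not being fixed. The primary 10-meter walk is not affected, since it has marked start and end points and a fixed aid. This is an inexpensive correction worth making, and not a threat to the trial's main result.

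**What to change.** In Section 8.2, under the TUG:

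1. Delete the parenthetical sentence.
2. State one rule for every visit: the clock starts at the first body movement from the prescribed seated posture and stops when the buttocks touch the chair seat. Name only that start event. Allowing the measurer's call as an alternative would bring back two starts, separated by the patient's reaction time.
3. Replace the daily-life aid lines with the 10-meter walk rule: the aid used on Day 0 is used at every later visit, and any deviation is recorded.

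This changes about three sentences and adds no test, visit or staff. The one small downside is that a patient who stops using an aid in daily life is still tested with it.

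These edits settle the interval and the aid only. The section also asks for one run at normal and one at maximum speed and then says "After two measurements, the smaller value (faster time) shall be adopted". Which speed supplies the endpoint value is a separate question, best settled in the same revision.

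### OABSS and the pain/numbness VAS ask about the time since the previous assessment, so baseline (28 days) and on-treatment scores (3 and 4 days) are not comparable and can be biased toward improvement

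*Protocol*

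**What the plan says.** Protocol section 8.2 (Evaluation points) schedules the OABSS and the VAS for pain and numbness on Days -28, 0, 3, 7, 14 and 28. The OABSS is used "to survey the period from the date of the last response to today". The VAS instruction reads "For the period from the time of the last evaluation to today, ask the patient to write the severity of the problem", on a 10 cm line. It does not say whether average or worst severity is to be marked.

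The OABSS items differ in kind. Item 1 asks "How many times do you typically urinate from walking in the morning to going to sleep at night", and item 2 asks about a typical night in the same way. Item 3 asks "How often do you have a sudden desire to urinate that is difficult to defer", and item 4 asks about leakage on the same answer scale. That scale runs from none (0) through "Less than once a week" (1) and at least weekly (2) to several times a day (5).

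Section 5.1 describes a single group with no placebo or control. Table 1 allows ±7 days at screening, −7 at admission and ±7 at the last visit. Neither scale appears among the objectives or endpoints in the Synopsis or in sections 3.1, 3.2 and 8.1.

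**The concern.** The recall period is set by the gap between visits, and that gap is longest at baseline and shortest during dosing. A patient whose symptoms do not change is asked about four weeks before treatment and about three or four days on treatment. Where a score depends on whether something happened in the window, the shorter window catches less of it.

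The rule also sits badly with the answer scale of items 3 and 4. A single episode in 3 days is an observed rate of 7/3 = 2.3 a week, and in 4 days 7/4 = 1.75 a week. A patient answering strictly for the window therefore moves from 0 to 2 and cannot reach the category for less than weekly.

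These are the only patient-reported bladder and pain measures scheduled. With no control group, nothing in the design separates a window artefact from a treatment effect. This is an explicit rule, not a detail left open, and analysis cannot repair it afterwards, because the question put to the patient already differs by visit.

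**Working it through.** **Inputs.** Assessment days and the recall rule come from section 8.2, the tolerances from Table 1 (−7 is read as up to 7 days early). The protocol states no recall length, episode rate or effect size for either scale, so there is no figure to reproduce. Episode rates, score cut-points and VAS variability below are assumptions, shown over a range.

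**Step 1: windows.** Differences between successive assessment days:

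- Day 0: 0 − (−28) = 28 days
- Day 3: 3 − 0 = 3 days
- Day 7: 7 − 3 = 4 days
- Day 14: 14 − 7 = 7 days
- Day 28: 28 − 14 = 14 days

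Baseline is 28/4 = 7 to 28/3 = 9.3 times as long as the on-treatment windows. With the tolerances, the Day 0 window runs from −7 − (−21) = 14 to 0 − (−35) = 35 days, and the Day 28 window from 21 − 14 = 7 to 35 − 14 = 21 days. Day -28 has no earlier response, so its window is undefined.

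**Step 2: chance of no episode, no true change.** With Poisson episodes, P(none) = exp(−rate per week × days/7).

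| Assumed rate | 28 d (Day 0) | 3 d (Day 3) | 4 d (Day 7) | 7 d (Day 14) | 14 d (Day 28) |
|---|---|---|---|---|---|
| 0.5 per week | 0.135 | 0.807 | 0.751 | 0.607 | 0.368 |
| 1 per week | 0.018 | 0.651 | 0.565 | 0.368 | 0.135 |
| 1 per day | <0.001 | 0.050 | 0.018 | 0.001 | <0.001 |

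At one a week, the share with no episode is higher at Day 3 than at Day 0 by 65.1 − 1.8 = 63.3, about 63 per 100 patients. At one a day the difference is about 5 per 100. Along the first two rows the chance of none jumps during dosing and then falls back, which would look like a response that fades after the drug stops.

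**Step 3: expected score on item 3 or 4, no true change.** Simulated, 400,000 windows per setting, scored on the rate observed in the window. Assumed cut-points: below 1 per week = 1; from 1 per week = 2; from 0.75 per day = 3; from 1.5 per day = 4; from 4.5 per day = 5.

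| Assumed rate | 28 d | 3 d | 4 d | Fall at Day 3 | Fall at Day 7 |
|---|---|---|---|---|---|
| 1 per 14 days | 1.01 | 0.39 | 0.50 | 0.62 | 0.51 |
| 1 per week | 1.55 | 0.71 | 0.89 | 0.84 | 0.66 |
| 2 per week | 1.96 | 1.21 | 1.47 | 0.75 | 0.49 |
| 5 per week | 2.44 | 2.19 | 2.50 | 0.25 | −0.06 |
| 1 per day | 2.93 | 2.66 | 2.94 | 0.27 | −0.01 |
| 3 per day | 4.00 | 4.01 | 4.04 | −0.01 | −0.04 |

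The spurious fall is about 0.5 to 0.85 points per item at these rates up to 2 episodes a week, and between 0 and 0.3 at about daily frequency or more.

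**Step 4: VAS, no true change.** Daily severity simulated as normal with assumed mean 5, limited to 0–10.

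- Marked as the period average: 5.0 in every window, so no shift.
- Marked as the period worst, daily SD 1: 7.01 (28 days), 5.85 (3 days), 6.03 (4 days). Falls of 1.16 and 0.98 cm.
- Marked as worst, SD 0.5: 6.01, 5.42, 5.51. Falls of 0.59 and 0.50 cm.
- Marked as worst, SD 2: 8.92, 6.68, 7.03. Falls of 2.24 and 1.89 cm.

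**Step 5: OABSS items 1 and 2.** These ask for a typical daily or nightly count, which does not depend materially on window length. They carry 2 + 3 = 5 of the 15 points.

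**The case against.** A reader might infer that the shrinking window by itself makes symptoms look improved on both scales. The documents do not support that. Items 1 and 2 ask what is typical. Items 3 and 4 ask for a frequency, and the daily categories can be judged in 3 or 4 days; at 5 episodes a week the expected Day 7 score even rises slightly. The VAS records severity, not a count of episodes, and a patient marking the average shows no shift. The phrase about pain at its worst is only the label at the right end of the line. All of this stands and limits the claim.

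The size is also uncertain. The protocol gives no episode rates, and the figure of 63 per 100 belongs to a rate at which the effect is large; in score terms it is 0.84 points on one item of a 15-point scale. Tolerances can narrow the contrast. If the admission questionnaire were done on Day -7 with dosing unmoved (an assumption) and screening fell on Day -21, the windows would be 14 and 10 days, and at one episode a week P(none) would be exp(−2) = 13.5% against exp(−10/7) = 24.0%, about 10 per 100. That is the mild extreme. It also shows that the window would differ between patients.

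The existing rule has a purpose: non-overlapping windows keep pre-treatment symptoms out of on-treatment answers. A fixed period no longer than the shortest gap between the visits kept does the same. Finally, a 7-day recall still cannot show a less-than-weekly rate directly. That is true, but the limit is then the same at every visit and does not bias change.

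**Conclusion.** The point holds in limited form. The unequal windows follow directly from section 8.2 and need no assumption: nominally 28 days at Day 0 against 3 and 4 days on treatment. Day 3 and Day 7 scores are therefore not comparable with Day 0 and, with no control group, can be biased toward improvement.

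The direction and size rest on assumptions the protocol cannot settle: infrequent episodes (about 2 a week or fewer) for items 3 and 4, and worst-severity marking for the VAS. Outside those conditions the shift is small or nil. It would go too far to say that an apparent improvement on these scales must be an artefact.

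Neither scale is a listed endpoint, and the primary 10-meter walk, which is timed on the day, is unaffected. This is a minor to moderate point.

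**What to change.** State one fixed recall period for each scale and use it at every visit. For example:

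- **OABSS:** the past 7 days, on Days -28, 0, 7, 14 and 28. Drop the Day 3 administration, because a 7-day recall there would reach back before dosing. The Day 7 recall then covers the dosing week, and no windows overlap.
- **VAS:** the past 24 hours at every visit, stating whether average or worst severity is to be marked.

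With equal windows, the change expected under no true effect is zero for every item, and the Day -28 window becomes defined.

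The cost is a change of questionnaire wording and the loss of one OABSS administration. Rare symptoms are captured less well than with a long recall, but equally so at every visit. No visit or test has to move.
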